### Ethics

This protocol was approved by the clinical research ethics committee of the Beijing Hospital of Traditional Chinese Medicine (2022BL02-028-03), where the study takes place. It has been registered with the Chinese Clinical Trial Registry (ChiCTR2200062453), which is listed in the WHO Registry Network. The trial complies with the principles of the Declaration of Helsinki and the principles of good clinical practice.

### Randomization and blinding

All the enrolled patients were included in the clinical trial according to the order of random table numbers from the numerical table generated by SAS software. The ratio of the experimental group to the control group is 1:1.

For blinding, the allocation code for each participant will be placed in opaque envelopes. The envelopes also contain details of the treatment options, possible adverse events, and emergency measures. The envelopes and treatment plans of each participant will not be accessible to all the researchers or participants. The drug and the placebo are similar, and the manufacturer will label the random codes on the package according to the principles of GCP.

Each coded experimental drug is accompanied by a corresponding emergency letter containing a slip of paper indicating the type of the coded drug to be used in the event of an emergency to break the blind. The emergency letters were sealed and sent to each clinical trial center with the corresponding numbered test drug, which is responsible for keeping it and should not be opened unless necessary. It should be opened by the investigator in the event of an emergency, or if the subject requires resuscitation, it is necessary to know what treatment the subject is receiving. Once opened, the numbered subject will be withdrawn from the trial and treated as a shedding case, and the investigator will record the reason for withdrawal on the case report form. All contingency letters will be retrieved with the case report form at the end of the trial for blinded review at the end of the trial.

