### Intervention

YQSJ (production batch number 181201) and YQSJ placebo (production batch number 181202) were produced and packed in a single batch by the Beijing Institute of Traditional Chinese Medicine. According to the preparation process, 1 g of the finished granules corresponds to approximately 1.67 g of crude herbal materials. Each bag of YQSJ contained 5 g of crude drug. The dosage is consistent with the recommended dosage in previous pharmacology studies and clinical practice (13). As tested, the drug conformed with the quality specified in the Chinese medicine standards published by the State Food and Drug Administration. Phytochemical analysis via LC-MS performed by Beijing Hexin Technology Co., Ltd. was used to identify the constituent compounds. The total ion chromatogram of Liquid chromatography-mass spectrometry, plant sources and compounds were presented in Supplementary Figures S1–S2 and Table S1–S2). Losartan will be purchased from the Pharmaceutical Branch of China Pharmaceutical Holdings Beijing Co., Ltd. (Unified Social Credit Identifier 91110101101297579G).

The experimental group will be treated with YQSJ 3 g twice a day and losartan 50 mg once a day, whereas the control group will be treated with YQSJ placebo 3 g twice a day and losartan 50 mg once a day. The patient's basic drug regimen remained unchanged. The treatment will last 8 weeks (56 days) in total, with follow-up visits every 2 weeks. Safety and efficacy indicators will be observed before and after 8 weeks of medication.

All participants will receive losartan as the background antihypertensive therapy throughout the study period. The use of other antihypertensive medications will be prohibited unless clinically necessary. If additional antihypertensive treatment is required due to uncontrolled blood pressure or safety concerns, the participant will be managed according to clinical judgment and may be withdrawn from the study if necessary. Medication adherence will be monitored through regular follow-up visits, drug accountability records, and patient self-reports to ensure compliance with the study protocol.

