### Endpoint measurements

#### Primary endpoint

The primary endpoint is the difference in drug efficiency between the two groups. Efficiency is defined as follows: blood pressure is reduced to a threshold set out in the Guiding Principles for Clinical Research of New Chinese Medicines (21). The level of glycosylated hemoglobin is decreased by at least 2% (22).

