### Statistical analysis

#### Sample size calculation

The sample size calculation was based on clinical research literature and preliminary clinical data. On the basis of the design of the superiority test, we assume that the efficiency of the placebo group is approximately 30%, and the efficiency of the experimental group is approximately 65%. In accordance with the statistical superiority test (superiority threshold of 0), *α* takes a unilateral value of 0.025. When the grouping ratio was 1:1 under the condition of 80% certainty, the control group and the experimental group needed 27 cases each as the evaluable number of cases. Considering the length of the district group and the 20% shedding rate, 36 patients were planned to be enrolled in each group, and a total of 72 patients were needed. PASS11 software was used to calculate the sample size.

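### Patients can be taken out of the trial for events linked to outcome while the sample size counts evaluable cases, so likely failures may be lost from the week-8 responder comparison

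*Protocol article*

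**What the plan says.** Three sections of the protocol article describe how a randomised patient leaves.

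- **Randomization and blinding.** Opening the emergency letter leads to mandatory exit: "Once opened, the numbered subject will be withdrawn from the trial and treated as a shedding case".
- **Recruitment, withdrawal criteria.** Allergic or serious adverse reactions, adverse events, intolerance and poor compliance are listed. No grade or relatedness limit is attached to adverse events.
- **Intervention.** If extra antihypertensive treatment is needed for uncontrolled blood pressure or for safety, "the participant will be managed according to clinical judgment and may be withdrawn from the study if necessary".

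Under Primary endpoint, "The primary endpoint is the difference in drug efficiency between the two groups", where efficiency is a responder definition built on blood pressure and glycosylated haemoglobin. Efficacy is assessed before treatment and after 8 weeks.

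Under Sample size calculation, the two arms "needed 27 cases each as the evaluable number of cases", and 36 per arm are enrolled to cover 20% shedding and the block length. The Data analysis section names tests. It names no analysis set and no rule for patients who leave.

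**The concern.** Code break, intolerance, poor compliance and rescue for uncontrolled blood pressure all arise after randomisation, and each is plausibly related to whether the patient would have responded at week 8. The exit described is from the trial. Nothing in the article says that visits or measurements continue afterwards, so a site that follows the text may never obtain week-8 blood pressure or HbA1c for these patients. A later analysis plan can impute those values but cannot recover them.

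If such patients are then left out as not evaluable, the responder rate loses failures from its denominator. The between-arm difference is biased when the loss differs by arm, and either direction is possible. If YQSJ is less well tolerated than placebo, more YQSJ failures go and the comparison is tilted towards YQSJ. If YQSJ lowers blood pressure, more control patients are rescued and may be removed, which tilts it against YQSJ. Because withdrawal after rescue is discretionary, who is counted also depends on individual judgement.

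**Working it through.** **1. The plan's own figure.** Inputs, all from Sample size calculation: "we assume that the efficiency of the placebo group is approximately 30%, and the efficiency of the experimental group is approximately 65" per cent; alpha "takes a unilateral value of 0.025"; "superiority threshold of 0"; power "under the condition of 80% certainty"; 1:1 allocation.

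Exact binomial enumeration of the unpooled z-test gives 78.2% power at 26 per arm and 80.6% at 27, so 27 is reproduced. Then 27/0.80 = 33.75, rounded up to 34, and 36 is consistent with rounding up for block length. At 36 enrolled, 36 × 0.80 = 28.8 remain evaluable, which is above 27. The sample size arithmetic is therefore not at fault. It does show that shedding cases were planned as not evaluable, so 30% and 65% are most naturally read as evaluable-case rates.

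**2. Size of the possible bias.** The documents give no withdrawal fraction by arm, so these are assumptions. Let r be the true response among all randomised patients, d the fraction removed, and s the response rate that the removed patients would have had. Then

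observed rate = (r − d·s) / (1 − d).

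Take r = 0.45 in both arms, so there is no true effect, with d = 0.05 in control and 0.20 in YQSJ.

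- All removed are failures (s = 0): 0.45/0.95 = 0.474 v 0.45/0.80 = 0.5625, a spurious +9 points.
- Removed patients respond at half the usual rate (s = 0.225): 0.43875/0.95 = 0.462 v 0.405/0.80 = 0.506, about +4 points.
- Removed patients are typical (s = 0.45): 0.45 v 0.45, no bias.
- Withdrawal fractions swapped between arms: the same sizes with a negative sign.

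**3. Effect on the test.** Simulation with 36 randomised per arm, failures removed, and a one-sided pooled z-test at 0.025:

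| True response, both arms | Removed, control v YQSJ | Observed rates | One-sided type I error |
|---|---|---|---|
| 45% | 5% v 20% | 47% v 56% | about 11% |
| 30% | 10% v 30% | 33% v 43% | 11–12% |
| 30% | 15% v 25% | 35% v 40% | 5.8% |
| 30% | 20% v 20% | 37.5% v 37.5% | 2.6% |

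Keeping all 36 per arm and counting the removed patients as failures brings the error back to 2.3–2.6% in these scenarios. This holds by construction, because the removed patients were assumed to be failures.

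**4. Cost of counting everyone.** Suppose 30% and 65% hold in evaluable patients and 20% per arm count as non-responders. The rates become 0.30 × 0.80 = 0.24 and 0.65 × 0.80 = 0.52, a difference of 28 points. With the pooled formula at 36 per arm and mean rate 0.38:

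z = [0.28·√36 − 1.96·√(2 × 0.38 × 0.62)] / √(0.24 × 0.76 + 0.52 × 0.48) = (1.680 − 1.345)/0.657 = 0.509, so power is 69%.

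Exact calculation gives 70% (pooled) or 73% (unpooled). For comparison, 29 evaluable patients per arm at 30% v 65% have exact power of 77% (pooled) or 78% (unpooled), so like for like the loss is about 5 to 7 points. Reaching 80% at 24% v 52% needs 44 (unpooled) to 46 (pooled) per arm, or 88 to 92 in total.

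**The case against.** The strongest reply is that the article never says the primary analysis is confined to evaluable cases. That is correct. The word evaluable occurs only in the sample size section, inflating enrolment for dropout is routine in trials analysed by intention to treat, and analysis sets are commonly left to a statistical analysis plan, which is not shown. A reader might infer that the plan counts only evaluable patients; the document does not establish it.

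Other strong readings also go further than the text:

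- That all these patients are shedding cases. The term is applied by name only to code breaks.
- That rescued patients are automatically withdrawn. The wording is permissive.
- That a rescued patient is a non-responder by definition. The blood pressure threshold sits in an external guideline that is not reproduced, and rescue is also allowed for safety reasons. Failure is likely, not certain.
- That the criterion about discrepancy from eligibility after inclusion catches patients whose blood pressure changes on treatment. It more naturally means ineligibility found after enrolment. Taken literally it would remove responders too.
- That safety follow-up is lost. Adverse events must be reported within 24 hours and the reason for withdrawal after a code break is recorded. The article does not say which data collection ends at withdrawal.

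It is also fair that the withdrawal fractions above are assumed, that some withdrawn patients would have responded, and that the trial is short and described as exploratory.

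What remains is that the exit rules are affirmative protocol text. They decide whether week-8 data exist at all, and that cannot be deferred to an analysis plan.

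**Conclusion.** The point holds as a risk created by rules that are written down. It does not hold as proof that failures are excluded from the primary analysis. Mandatory exit after code break, listed exit for adverse events, intolerance or poor compliance, and discretionary exit after rescue, combined with evaluable-case sizing, can remove likely failures from the week-8 comparison.

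The bias depends on the imbalance between arms and on how many of the removed patients would have failed. In the illustrations it runs from zero to about 9 points in either direction, and the one-sided error rises from 2.5% to between 6% and 12% where more YQSJ failures are removed. Equal withdrawal of failures in both arms leaves the error under no effect essentially intact. The protocol itself allows for 20% shedding, so fractions of this order are within its own expectations.

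**What to change.** 1. Reconcile the Recruitment, Randomization and blinding, and Intervention sections on whether withdrawal is mandatory or discretionary for each trigger. Which clinical rule is right is for the investigators, and none is proposed here.
2. Whatever is decided clinically about study drug, state that week-8 blood pressure, HbA1c and safety data are still collected unless the patient withdraws consent.
3. Make the primary analysis all randomised patients, as randomised, with a prespecified rule for withdrawn, rescued or unblinded patients. Counting a missing week-8 result as non-response is one example; other rules can be defended if fixed in advance, before unblinding.
4. Move the evaluable-case comparison to a sensitivity analysis, and report withdrawals by arm and reason.

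The cost is wording plus continued use of a visit that already exists. The article reports 40 of 72 patients recruited, so follow-up can still be protected for the 32 to come and for any not yet at week 8; the analysis rule can apply to all. The power cost should be stated openly: about 70% at 36 per arm, against the planned 80%, if 20% per arm count as failures and 30%/65% are evaluable-case rates. Restoring 80% would need 88 to 92 patients in total.

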### Intervention

YQSJ (production batch number 181201) and YQSJ placebo (production batch number 181202) were produced and packed in a single batch by the Beijing Institute of Traditional Chinese Medicine. According to the preparation process, 1 g of the finished granules corresponds to approximately 1.67 g of crude herbal materials. Each bag of YQSJ contained 5 g of crude drug. The dosage is consistent with the recommended dosage in previous pharmacology studies and clinical practice (13). As tested, the drug conformed with the quality specified in the Chinese medicine standards published by the State Food and Drug Administration. Phytochemical analysis via LC-MS performed by Beijing Hexin Technology Co., Ltd. was used to identify the constituent compounds. The total ion chromatogram of Liquid chromatography-mass spectrometry, plant sources and compounds were presented in Supplementary Figures S1–S2 and Table S1–S2). Losartan will be purchased from the Pharmaceutical Branch of China Pharmaceutical Holdings Beijing Co., Ltd. (Unified Social Credit Identifier 91110101101297579G).

The experimental group will be treated with YQSJ 3 g twice a day and losartan 50 mg once a day, whereas the control group will be treated with YQSJ placebo 3 g twice a day and losartan 50 mg once a day. The patient's basic drug regimen remained unchanged. The treatment will last 8 weeks (56 days) in total, with follow-up visits every 2 weeks. Safety and efficacy indicators will be observed before and after 8 weeks of medication.

All participants will receive losartan as the background antihypertensive therapy throughout the study period. The use of other antihypertensive medications will be prohibited unless clinically necessary. If additional antihypertensive treatment is required due to uncontrolled blood pressure or safety concerns, the participant will be managed according to clinical judgment and may be withdrawn from the study if necessary. Medication adherence will be monitored through regular follow-up visits, drug accountability records, and patient self-reports to ensure compliance with the study protocol.

To minimize the impact of potential confounding factors, all participants will receive standardized lifestyle recommendations, including diet and physical activity guidance, based on current hypertension management guidelines. Participants will be instructed to maintain stable lifestyle habits during the study period and to avoid significant changes in diet, exercise, or weight. Body weight will be recorded at baseline and monitored during follow-up visits. Any substantial changes will be documented and considered in the analysis.

### Endpoint measurements

#### Primary endpoint

The primary endpoint is the difference in drug efficiency between the two groups. Efficiency is defined as follows: blood pressure is reduced to a threshold set out in the Guiding Principles for Clinical Research of New Chinese Medicines (21). The level of glycosylated hemoglobin is decreased by at least 2% (22).

#### Secondary endpoints

24-h blood pressure indicators: average SBP, DBP, mean arterial pressure (MAP), blood pressure variability and circadian blood pressure amplitudeGlucose metabolism indicators: fasting blood glucose, 2 h postprandial blood glucose, glycosylated hemoglobin, CMI = WHtR × [TG (mmol/L)/HDL-C (mmol/L), WHtR = waist circumference (cm)/height (cm) (23), HOMA-IR = FBG (mmol/L) × FINS (μU/mL)/22.5 (24)Lipid metabolism indicators: triglycerides, cholesterol, LDL, HDLVascular damage indicators: vascular endothelial function markers, brachial and ankle artery pulse wave velocity, ankle-brachial indexThe oxidative stress indicators: superoxide dismutase (SOD) and malondialdehyde (MDA).Major adverse cardiovascular events (MACEs) and disease regression within 6 months of treatment initiationSafety indicators: Hepatic and renal function, routine blood results and routine urine results will be assessed at baseline and at the treatment endpoint.

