### Recruitment

Participants will recruit from Beijing Hospital of Traditional Chinese Medicine through notices in hospital and newspapers. Advertisement approved by the Research Ethics Committee will be used to promote enrollment. The principal investigator, together with a well-trained attending physician, will identify potential patients on the basis of the eligibility criteria. All the included participants were informed face to face of the entire study according to the Research Ethics Committee and voluntarily signed the informed consent form.

The eligibility criteria for the study participants were as follows:

Inclusion criteria: patients who met all of the following criteria.
Understand the process of this trial and provide informed consent.Patients were diagnosed with impaired fasting glucose, abnormal glucose tolerance or type 2 diabetes mellitus in accordance with the ADA standard (3), and HbA1c < 8% within the past 2 weeks.The patient was diagnosed with primary hypertension (grade 1–2) in accordance with the AHA standard (1). It is defined as systolic blood pressure (SBP) of 140–179 mmHg and/or diastolic blood pressure (DBP) of 90–109 mmHg.Male aged between 18 and 75 years.Exclusion criteria: Patients who met any of the following criteria.
Severe infection, trauma and/or recent or planned surgery.Severe conscious impairment, severe cognitive dysfunction, or severe psychiatric disorders;Those with other comorbidities, such as chronic kidney disease and liver disease (hepatic inadequacy: alanine amino transferase or alkaline phosphatase levels more than twice the upper normal limit). Renal inadequacy: serum creatinine level ≥133 mmol/L)Withdrawal criteria: Patients who met any of the following criteria.
Discrepant the eligibility criteria after inclusion.The participants were asked to withdraw.Allergic reactions, serious adverse reactions, adverse events, or intoleranceUnable to perform the test as needed (poor compliance).

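### HOMA-IR is scored in every participant although insulin-treated type 2 diabetes is not excluded; in anyone on exogenous insulin the index cannot be read as insulin resistance

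*Protocol article*

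**What the plan says.** All references are to the protocol article.

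- **Secondary endpoints** gives the index as "HOMA-IR = FBG (mmol/L) × FINS" (μU/mL) divided by 22.5, listed with the glucose metabolism indicators. No subset of participants is named. The Abstract lists insulin resistance indicators as an endpoint group of their own.
- **Recruitment** admits patients with "impaired fasting glucose, abnormal glucose tolerance or type 2 diabetes mellitus in accordance with the ADA standard", with HbA1c below 8%. The exclusion list begins with "Severe infection, trauma and/or recent or planned surgery" and goes on to disorders of consciousness, cognition and mental health and to other comorbidities such as kidney and liver disease. Insulin treatment appears in neither list.
- **Intervention** (and Design) says "The patient's basic drug regimen remained unchanged". The only drug restriction concerns blood pressure treatment: "The use of other antihypertensive medications will be prohibited unless clinically necessary".
- **Data analysis** compares continuous variables by t test or, if not normally distributed, by rank sum test. The only covariate it names is baseline blood pressure. It has no exclusion, stratum or adjustment for insulin use.

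**The concern.** The product of fasting glucose and fasting insulin indexes resistance only if the measured insulin is the body's own response to that glucose. In a patient who injects insulin this no longer holds. If the assay detects the injected product, the index is raised by the drug. If it does not, the index misses insulin that is circulating and acting on glucose. In both cases a number comes out and is pooled with valid ones.

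This matters here because insulin resistance is central to the proposed mechanism. The Backgrounds section cites a lower insulin resistance index in diabetic mice and a possible action on the IRS-1/PI3K/AKT pathway, and the Abstract promises to explore mechanism. HOMA-IR is the only index among the listed secondary endpoints that uses insulin, so the mechanistic reading in patients depends largely on it.

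**Working it through.** The plan states no figure for this index, so there is none to reproduce. The check sets the sections side by side and then looks at how the formula behaves.

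**Step 1: can an insulin user be scored?**

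- Entry: type 2 diabetes qualifies, with no condition on treatment (Recruitment).
- During the trial: the background regimen is kept, and only other antihypertensives are restricted (Intervention).
- Endpoint: the formula carries no restriction (Secondary endpoints).
- Analysis: insulin use is not handled (Data analysis).
- Alternative measure: C-peptide, or any other marker of endogenous secretion, is not mentioned.

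So the article as written would score any insulin user who entered.

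**Step 2: what does the formula return?**

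HOMA-IR = FBG × FINS / 22.5, so it is directly proportional to measured insulin. The documents give no insulin or glucose levels. The following inputs are therefore assumptions for illustration: FBG of 6, 7 or 8 mmol/L, endogenous insulin of 10 μU/mL held fixed, and 0, 5, 10 or 20 μU/mL of injected insulin read by the assay.

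| FBG (mmol/L) | +0 | +5 | +10 | +20 |
|---|---|---|---|---|
| 6 | 2.67 | 4.00 | 5.33 | 8.00 |
| 7 | 3.11 | 4.67 | 6.22 | 9.33 |
| 8 | 3.56 | 5.33 | 7.11 | 10.67 |

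For example, 7 × 10 / 22.5 = 3.11 and 7 × 30 / 22.5 = 9.33. In each row the patient's own insulin and glucose are the same, yet the index triples from the first column to the last because measured insulin goes from 10 to 30. Holding endogenous insulin fixed is a simplification, since injected insulin may also suppress it. That makes the value harder still to interpret.

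**Step 3: what reaches the group comparison?**

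That depends on the number of insulin users, their split between the arms of 36, the assay and the spread of the index. None of these is in the documents, so no shift in the group difference is calculated. Randomisation balances insulin users in expectation, which leaves added variance and dilution as the expected effect.

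**The case against.** The strongest reply is that the premise rests on silence. The article never says that insulin users are enrolled. It condenses a fuller protocol, which may list drug exclusions or define an analysis set for this index. The HbA1c limit and the admission of prediabetes may also keep insulin users few. This stands as a limit on size: the number is unknown and could be zero. It does not remove the point, because the article fixes both the population and the formula, and together they give an uninterpretable value in one subgroup.

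Three stronger readings are tempting, and the documents do not support them.

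- **That the treatment comparison is biased.** Allocation is random, so a directional error needs a chance imbalance, which is possible with 36 per arm but not expected.
- **That a few extreme values would dominate the result, or mimic a treatment effect.** Every input for such a claim would have to be assumed. Data analysis also sends non-normal variables to the rank sum test, which limits the pull of extreme values.
- **That the index in these patients reflects injected insulin alone.** The measured value is a mixture. Laboratory tests names kits for the oxidative stress markers but describes no insulin assay, so the degree of mixing cannot be judged.

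It is also fair to say that the trial is declared exploratory and that this is one of many secondary measures.

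**Conclusion.** The point holds as a minor one. HOMA-IR as defined is not valid in participants on exogenous insulin, and nothing in the article keeps them out of its calculation. The expected consequence is noise and lost interpretability in a single secondary endpoint; a distorted group difference would need a chance imbalance. The conclusion assumes that at least one insulin-treated patient is enrolled and that no document outside the article already restricts this analysis. The illustrative values show how the formula responds to measured insulin. They do not estimate the effect on the trial's result.

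**What to change.** Add to the HOMA-IR entry in Secondary endpoints that the index is analysed in participants not using exogenous insulin at baseline, that the number left out is reported per arm, and that these participants stay in every other endpoint.

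The restriction should rest on baseline use only. Also dropping those on insulin at week 8 looks natural, but starting insulin during the trial can depend on glycaemic response and hence on treatment, so that rule would select on a post-randomisation event. Participants who start insulin after randomisation should stay in the main comparison, be reported by arm and be addressed in a sensitivity analysis.

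The cost is small. Concomitant drugs are already recorded at each evaluation (Data collection and management), so no new data are needed and eligibility does not change. The one loss is a slightly smaller sample for this index. Trial status reports 40 patients recruited and completion by June 2026, so the rule can still be set before unblinding. Set later, it could look like selective exclusion.

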### Design

This is an exploratory study with a randomized, double-blind, placebo-controlled design. All protocol modifications were made before participant enrollment to improve feasibility, ensure operational consistency, and comply with ethics requirements. They were planned and implemented by the study team, reviewed and approved by the ethics committee, as detailed in Supplementary Material.

After screening and voluntarily signing the informed consent form, 72 participants recruited from the Beijing Hospital of Traditional Chinese Medicine will be randomly and evenly assigned into the experimental and control groups on the basis of the randomized numerical table generated by SAS software.

The experimental group will be treated with YQSJ 3 g twice a day and losartan 50 mg once a day, whereas the control group will be treated with YQSJ placebo 3 g twice a day and losartan 50 mg once a day. The patient's basic drug regimen remained unchanged. The treatment will last 8 weeks (56 days) in total, with follow-up visits every 2 weeks. Safety and efficacy indicators will be observed before and after 8 weeks of medication (Figure 1).

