### Data collection and management

Data for each participant will be recorded in a case report form. Patients are required to attend the assessment every 14 days and finish the trial with 5 evaluations, including the enrollment evaluation (0 days, 14 ± 2 days, 28 ± 5 days, 42 ± 5 days, and 56 ± 5 days). Each evaluation included general demography, relevant medical history and diagnosis, safety evaluation, blood pressure assessment in the consultation room, symptom improvement assessment, target organ damage assessment, cardiovascular risk factor assessment, and other methods, such as adverse event recording, combined drug recording, and compliance assessment, as shown in Figure 2. Baseline blood pressure will be measured using standardized procedures, and the average of at least two measurements will be recorded for each participant.

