#### Data analysis

SPSS 15.0 (PN: 32119001, SN: 5045602) will be used for statistical analysis. The measurement data are expressed as the means ± standard deviations. Between-group comparisons of two groups of normally distributed and variance-aligned continuous variables were performed via t tests. Comparisons between groups of two normally distributed continuous variables with chi-square variance between each stratum will be performed via analysis of variance (ANOVA) with randomized area group design data, and two-by-two comparisons between multiple groups will be performed via the SNK-q test. Comparisons between groups of nonnormally distributed continuous variables will be performed via the rank sum test. Comparisons between groups of count data were performed via the chi-square test, and Fisher's exact probability test will be used when the expected frequency is <5. Major adverse cardiac events will be evaluated via Cox regression analysis. *P* < 0.05 is considered a statistically significant difference. Baseline blood pressure levels will be included as covariates in the statistical analysis to minimize potential confounding effects.

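### MACE and disease regression carry a 6-month window, but the stated visit schedule ends the trial at about day 56, so a 6-month result would be unsupported unless the two are reconciled

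*Protocol article*

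**What the plan says.** Three parts of the protocol article bear on this endpoint.

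- **Endpoint.** Secondary endpoints lists major "adverse cardiovascular events (MACEs) and disease regression within 6 months of treatment" initiation. The Abstract also names MACE as a secondary endpoint, without a window.
- **Schedule.** Design gives the course: "The treatment will last 8 weeks (56 days) in total, with follow-up visits every 2 weeks". Data collection and management adds: "Patients are required to attend the assessment every 14 days and finish the trial with 5 evaluations, including the enrollment evaluation". It lists the five as "0 days, 14 ± 2 days, 28 ± 5 days, 42 ± 5 days, and 56 ± 5 days". Design also says: "Safety and efficacy indicators will be observed before and after 8 weeks of medication".
- **Analysis.** Data analysis says: "Major adverse cardiac events will be evaluated via Cox regression analysis". It states no censoring date.

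The only other 6-month period in the text is the time allowed for assaying frozen samples, under Laboratory tests. It has nothing to do with following participants. Limitations describes follow-up as relatively short but gives no length.

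**The concern.** The endpoint needs each participant's status up to 6 months after treatment starts. The schedule says that participation is over after the fifth evaluation, at about 8 weeks. A condensed article may leave out how follow-up is done. This one is not silent, though: it gives the number of evaluations, dates each one, and says that patients complete the trial with them. Two current statements therefore disagree.

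At stake is what the report may claim. If the schedule is followed, a MACE result labelled as 6-month would rest on about 8 weeks of planned observation. Later events would enter only if they happened to come to the investigators' notice, so ascertainment after the last visit would be incomplete. A statement that no MACE occurred within 6 months could not be supported. Disease regression is in a worse position, because a status at 6 months cannot be read from a visit at week 8.

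**Working it through.** The plan gives no figure for coverage of the window, so there is none to reproduce. The check compares the stated window with the stated visits.

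**Inputs**
- Window: 6 months from treatment initiation (Secondary endpoints). The article does not convert this to days. I assume 182 days, with a range of 180 to 184.
- Last evaluation: day 56 ± 5, that is, day 51 to day 61 (Data collection and management).
- Planned size: 72 participants (Design).

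**Share of the window without planned observation** = 1 − (day of last visit ÷ days in 6 months)

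| Last visit | Window (days) | Observed | Not observed | Days not observed |
|---|---|---|---|---|
| Day 56 (nominal) | 182 | 56/182 = 30.8% | 69.2% | 126 |
| Day 61 (latest) | 180 | 61/180 = 33.9% | 66.1% | 119 |
| Day 51 (earliest) | 184 | 51/184 = 27.7% | 72.3% | 133 |

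So 66% to 72% of the window has no planned observation. To cover the whole window, follow-up would have to run 180 − 56 = 124 to 184 − 56 = 128 days past the nominal last visit, or roughly four more months.

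**What this does to the two components**
- *MACE.* A Cox model can still be fitted. Every participant without an event would be censored at the last visit, so the hazard ratio would describe about 8 weeks.
- *Disease regression.* This is a status, not an event time that can be censored. Without an assessment at 6 months, its 6-month value is not collected.

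**How much information either window could give.** The article states no MACE rate. I therefore assume annual rates of 1% to 10%, with all 72 followed throughout and both arms together:
- to day 56, expected events = 72 × rate × 56/365.25, which gives 0.11 at 1% and 1.10 at 10%;
- to 6 months (182.6 days), expected events = 72 × rate × 182.6/365.25, which gives 0.36 at 1% and 3.60 at 10%.

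Across that range, neither window yields enough events for a useful hazard ratio.

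**The case against.** The strongest reply is that the decisive page is missing. The flowchart and the schedule of assessments (Figures 1 and 2) are not shown, and a 6-month contact would most naturally appear there or in the full protocol. The five evaluations might also be only the on-site visits, which would leave room for remote follow-up of events. The before-and-after timing in Design concerns measured indicators, whereas MACE has a window of its own. The remark on short follow-up in Limitations fits 8 weeks and 6 months equally well.

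Much of this stands. A reader might infer that the later months are never observed. The documents do not support that, because the figures are unseen; they show only that the visible text plans no observation there. The remark in Limitations is not evidence either way. But the reply does not remove the conflict. The text says that patients complete the trial with five dated evaluations, and a later contact in Figure 2 would contradict it.

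Two further inferences are tempting and go too far:
- *That the endpoint cannot be derived at all.* MACE to week 8 can be derived. Only the 6-month versions lack data.
- *That missed late events would differ by arm.* The trial is double-blind and placebo-controlled, and the documents show no mechanism for such a difference. Incomplete ascertainment is problem enough without it.

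It is also fair to say that the consequence is limited. This is one of many secondary endpoints in a trial that calls itself exploratory, with few events likely under either window.

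**Conclusion.** The point holds as an internal contradiction. The 6-month window for MACE and disease regression does not match a schedule that ends participation at about day 56. On that schedule, 66% to 72% of the window has no planned observation for any participant. The Cox analysis would give a result to about week 8 under a 6-month label, and 6-month disease regression would not be collected.

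This rests on taking 6 months as 180 to 184 days and on reading the visible text as it stands. If Figure 2 or the full protocol contains a 6-month contact, the data may exist. The fault would then lie in the description of the schedule, which would still need correcting. The documents do not settle which statement is the wrong one.

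The matter should be corrected, but it does not threaten the trial's main result: neither the primary endpoint nor the sample size depends on it.

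**What to change.** Reconcile Secondary endpoints, Data collection and management, Data analysis and Figure 2 by a documented amendment before unblinding, so that the window is not chosen after events by arm are known. There are two ways to do it.

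1. **Align the endpoint with the visits.** Restate it as MACE and disease status from randomisation to the week-8 visit, and report MACE as counts per arm instead of relying on a Cox model. The cost is a shorter and less ambitious endpoint.
2. **Align the visits with the endpoint**, if 6 months is intended and a contact is planned. State in Data collection and management, and show in Figure 2, one brief contact at 6 months, made blind to allocation, for every randomised participant, including those who stopped early. State the censoring date for the Cox analysis to match. The cost is up to 72 contacts.

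A reader might take the first option for a change of wording only. It is more than that. Trial status reports a start in January 2024 and 40 patients recruited, which leaves 72 − 40 = 32 of the planned number to enrol at that point. Shortening a registered trial's secondary endpoint at that stage is a change of endpoint and should be recorded as one. Under the second option, some of those already recruited may have passed 6 months. The report should say how many were contacted late, because their information would be retrospective.
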